The primary aim of this RCT is to determine if video-conferencing consultations are non-inferior to face-to-face consultations with a physiotherapist for improving knee pain on walking and/or physical function at 3 months (primary time-point) and 9 months (secondary time-point), in people with knee OA. We hypothesise that video consultations are not inferior for improving knee pain on walking and/or physical function compared to face-to-face care in people with knee OA. Secondary aims are to compare the clinical effectiveness (health-related quality of life, therapeutic relationship, global ratings of change, satisfaction with care, self-efficacy, physical activity levels), cost-effectiveness (participant-level travel time and travel-related costs, health care usage) and convenience of video-conferencing consultations to face-to-face consultations, as well as explore potential moderators of treatment effect.

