#### Secondary outcomes

For quality of life, physical activity and self-efficacy, change scores are calculated using data measured at baseline, 3 months and 9 months. Other secondary outcomes are measured at time-points as indicated below:

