### Economic evaluation

A health economist will oversee assessment of incremental direct and indirect costs of video consultations compared to face-to-face. Primary evaluation will be between-group difference in knee-related health care costs and quality-adjusted life years (QALYs) using generalised linear models to adjust for baseline. Non-inferiority in QALYs will be demonstrated if the lower bound of the two-sided 95% CI for between-group difference of the AQoL-6D is above − 0.08 (half a SD). If one type of consultation is superior but costs more, QALYs will be calculated using area under the curve over 9 months. The incremental cost per QALY as the ratio of difference in mean cost to difference in mean QALYs, and net benefits as the difference in QALYs times the social value of a QALY minus the difference in cost, will then be calculated. If non-inferiority of QALYs is demonstrated, then inferiority in terms of cost (and net benefits) will then be assessed if the lower bound of the two-sided 95% CI for between-group difference exceeds zero. In a secondary analysis, the cost of patient time will be included as an additional cost component.

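### The economic plan makes QALYs a primary outcome, yet ties their only stated calculation, and net benefit, to a result that is unlikely if the two modes are similar

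*Protocol article*

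**What the plan says.** All the relevant rules stand in the Economic evaluation section.

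1. The primary comparison carries no condition: "Primary evaluation will be between-group difference in knee-related health care costs and quality-adjusted life years (QALYs) using generalised linear models to adjust for baseline".
2. Non-inferiority is judged on the utility score: "Non-inferiority in QALYs will be demonstrated if the lower bound of the two-sided 95% CI for between-group difference of the AQoL-6D is above" -0.08, described as half an SD.
3. The QALY method is conditional: "If one type of consultation is superior but costs more, QALYs will be calculated using area under the curve over 9 months". The next sentence continues from it. It defines the cost-per-QALY ratio and then "net benefits as the difference in QALYs times the social value of a QALY minus the difference in cost, will then be calculated".
4. A second route begins: "If non-inferiority of QALYs is demonstrated, then inferiority in terms of cost (and net benefits) will then be assessed". The criterion is that the lower bound of the two-sided 95% CI for the between-group difference exceeds zero.

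Under Secondary outcomes the data schedule is: "For quality of life, physical activity and self-efficacy, change scores are calculated using data measured at baseline, 3 months and 9 months". Health service usage is recorded at baseline, 3, 6 and 9 months. The Background names cost-effectiveness as a secondary aim, again without condition.

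**The concern.** Rule 1 needs a QALY difference in every case. Rule 4 needs one whenever non-inferiority is shown, because net benefit is built from it. Rule 3 is the only place that says how QALYs are obtained, and it applies only when the better mode is also the dearer one.

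The trial hypothesises that video is not inferior, so the non-inferiority route is the expected one, and the QALY calculation is not triggered there. An analyst who followed the text literally would have a cost comparison with no defined QALY or net-benefit estimate beside it. A modest health difference, too small to be significant, could then drop out of the economic conclusion.

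The criterion in rule 4 is a second problem, because a positive difference is bad for cost and good for net benefit.

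**Working it through.** **The plan's own figure.** The article gives no power for the economic evaluation, so the sample size is checked first to fix the number analysed. Per arm, n = 2 × (1.96 + 1.2816)² × SD² × (1 - 0.3²) / margin².
- Pain: 2 × 10.507 × 2.8² × 0.91 / 0.95² = 166.1, so 167; 167 / 0.85 = 196.5, so 197.
- Function: 2 × 10.507 × 15² × 0.91 / 5.44² = 145.4, so 146; 146 / 0.85 = 171.8, so 172.

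Both match the article. About 167 per arm are therefore analysed after 15% loss.

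**Inputs for the AQoL-6D.** The margin of 0.08 is half an SD, so SD = 0.08 / 0.5 = 0.16. The baseline correlation r for this score is not given; 0 to 0.8 is assumed. The section does not define 'superior'; it is taken here as a 95% CI that excludes zero.

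**Standard error.** SE = 0.16 × √(1 - r²) × √(2/167).
- r = 0: 0.0175, CI half-width 1.96 × 0.0175 = 0.0343.
- r = 0.8: 0.0105, CI half-width 0.0206.

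**Chance that either mode is superior**, Φ(d/SE - 1.96) + Φ(-d/SE - 1.96):

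| True difference d | r = 0 | r = 0.8 |
|---|---|---|
| 0 | 5.0% | 5.0% |
| 0.02 | 20.8% | about 48% |

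These are upper bounds for the full condition, because the superior mode must also cost more.

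**Chance of passing the -0.08 test** (r = 0), Φ((0.08 + d)/SE - 1.96): 99.5% at d = 0 and 92.9% at d = -0.02.

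**How the routes fit together.** If neither mode is superior, the estimate is no lower than -0.0343, so the lower bound is no lower than -0.0686, which is above -0.08. With these inputs every result in which neither mode is superior (95% of trials under equality) goes to the non-inferiority route without triggering the QALY calculation.

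**What could be left out.** An observed deficit for video of up to 0.034 (r = 0) or 0.021 (r = 0.8) would be both non-significant and non-inferior. If it builds linearly from zero at baseline to 3 months and is then held to 9 months, the area is 0.034 × (0.125 + 0.5) = 0.021 QALY, or 0.021 × 0.625 = 0.013 QALY. The article gives no monetary value of a QALY, so this is not converted to money.

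**Sign of the rule.** Take differences as video minus face-to-face, the direction used for the co-primary outcomes. A lower bound above zero for cost means that video costs more, which is inferiority. Net benefit is the QALY difference times its value, minus the cost difference. A lower bound above zero for net benefit means that video is better.

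**The case against.** The strongest reply is that the primary sentence already promises a QALY difference with no condition, and that the word 'only' is not in the text. That stands. A reader might infer that QALYs are never calculated on the non-inferiority route, or that the likeliest results give no cost-effectiveness answer. The documents do not support either reading. The primary comparison is always planned, cost is still compared after non-inferiority, and a mode that is both better and cheaper needs no ratio. What remains is a contradiction between the unconditional outcome and its conditional method.

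It could also be said that the AQoL-6D difference can stand in for QALYs, since the non-inferiority test treats the two as one. It cannot go into the net-benefit formula as it is. A difference of 0.08 held for 9 months is 0.08 × 0.75 = 0.06 QALY, and one that builds linearly to 3 months and is then held is 0.08 × 0.625 = 0.05 QALY.

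The condition may be meant in the ordinary sense that mean effects and costs trade off, with no significance test. That is possible, since 'superior' is undefined here. The percentages above depend on the other reading, but the contradiction does not.

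Finally, methods for joint uncertainty, such as bootstrap intervals or acceptability curves, commonly belong in a fuller plan. Their absence from an article is no fault and forms no part of this point.

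**Conclusion.** The point holds as an internal contradiction in what the article states. The QALY difference is an unconditional primary economic outcome. Its only stated calculation, the ratio and net benefit hang on one mode being superior and dearer, and the non-inferiority route nevertheless requires net benefit.

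On the stated assumptions (SD 0.16, 167 per arm, 'superior' as a CI excluding zero), the superiority half of the condition is met in about 5% of trials under equality. At a true difference of 0.02 it is met in about 21%, rising to about 48% with a baseline correlation of 0.8. The -0.08 test is passed in about 99.5% under equality, so the expected route is the one on which the QALY calculation is not triggered.

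Separately, and without any assumption about SD, one sign rule cannot show inferiority for both cost and net benefit.

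Cost-effectiveness is a secondary aim and the co-primary analyses are unaffected, but the text should be put right before the economic analysis is done.

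**What to change.** - Calculate area-under-the-curve QALYs over 9 months, and costs, for all randomised participants, whatever the superiority or non-inferiority result.
- Always report the baseline-adjusted incremental cost, incremental QALYs and net benefit, each with a confidence interval.
- Keep the condition only for presenting the cost-per-QALY ratio, which is informative when the mean differences in cost and QALYs trade off.
- Give cost and net benefit separate rules. With differences as video minus face-to-face, a lower bound above zero shows higher cost for video; for net benefit a lower bound above zero shows an advantage for video and an upper bound below zero a disadvantage.

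The cost is a wording change and a little more analysis. The AQoL-6D and health service data are already collected at the times needed, and the sample size does not change.

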Consistent with OARSI guidelines [52], non-inferiority will be assessed using the per-protocol dataset (including only those randomized participants who attended ≥3 consultations). Between-group differences in mean change in pain and function (baseline minus follow-up) will be compared using linear regression modelling adjusted for baseline and the stratifying variable of physiotherapist. If a physiotherapist treats participants at two locations, two separate terms for that physiotherapist, corresponding to each location, will be included. Non-inferiority will be demonstrated if the lower bound of the two-sided 95% CI for between-group difference (video-conferencing minus face-to-face) is above − 0.95 for change in pain and/or − 5.44 for change in function, at 3 months. 95% CIs correspond to testing the null hypothesis of non-inferiority at a one-sided significance level of 2.5%. Due to difficulties with their interpretation, *p*-values associated with non-inferiority hypotheses are not commonly reported and will not be reported here [53]. Multiple imputation will be used to impute missing data, and an intention-to-treat analysis (including all participants in their randomised groups) will be conducted to help assess robustness of conclusions (sensitivity analysis). Given that participants with knee OA seek physiotherapy care for different reasons, we will interpret and report findings transparently and separately for each co-primary outcome. For example, if we demonstrate non-inferiority of video consultations with respect to function but not pain, we will conclude that video consultations are non-inferior to face-to-face care for improving function but are inferior for pain relief in people with knee OA. Patients seeking care, and physiotherapists delivering care, will then be fully informed about benefits, and limitations, of video consultations compared to face-to-face care with respect to the different co-primary outcomes. If non-inferiority of a co-primary outcome is demonstrated, superiority of the outcome will then be assessed using the intention-to-treat dataset and declared if the lower bound of the two-sided 95% CI for between-group difference exceeds zero.

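### One confidence-interval rule is used to assess inferiority on both cost and net benefit, although the plan's own formula makes the two run in opposite directions

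*Protocol article*

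**What the plan says.** All of this is in the protocol article, mainly under Economic evaluation.

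- **Contrast.** The section is to assess "incremental direct and indirect costs of video consultations compared to face-to-face". It does not restate the order of subtraction for costs. The Statistical analysis plan section fixes the order for the co-primary outcomes, through the "two-sided 95% CI for between-group difference (video-conferencing minus face-to-face").
- **First step.** "Non-inferiority in QALYs will be demonstrated if the lower bound of the two-sided 95% CI for between-group difference of the AQoL-6D" lies above a margin of −0.08, described as half a standard deviation.
- **Net benefit.** The article defines "net benefits as the difference in QALYs times the social value of a QALY minus the difference in cost".
- **Decision rule.** If QALY non-inferiority is shown, "inferiority in terms of cost (and net benefits) will then be assessed if the lower bound of the two-sided 95% CI" meets the stated condition. That condition, in full, is that the lower bound of "the two-sided 95% CI for between-group difference exceeds zero". One rule covers both quantities, and net benefit has no rule of its own.

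**The concern.** Cost is a quantity where lower is better. Net benefit, as defined here, is one where higher is better. A single bound with a single label cannot be correct for both.

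The Statistical analysis plan section uses the same bound, a lower limit above zero, to declare superiority on the co-primary change scores, where a larger value is better. Net benefit is also a larger-is-better quantity, yet in the economic section the same result is called inferiority.

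At stake is the direction of the net-benefit conclusion. Applied literally, the rule gives an adverse label to video when its interval shows a gain, and gives no label when the interval shows a loss.

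**Working it through.** The plan prints no figure on this point, so the check is one of sign, followed by an illustration.

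**1. Sign check (article's definitions only).** Write dC and dQ for the differences in cost and QALYs, video minus face-to-face, and λ for the social value of a QALY. The article's definition is NB = λ·dQ − dC.

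- Lower limit of dC > 0: video costs more. Calling video inferior on cost is right.
- Lower limit of NB > 0: video yields more net benefit. Calling video inferior on net benefit is wrong.

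**2. Can another reading rescue it?** There are four combinations of subtraction order and label. In each, the rule is that the lower limit is above zero, and the label refers to video.

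| Contrast | Label | Cost | Net benefit |
|---|---|---|---|
| video − face-to-face | inferior | right | wrong |
| video − face-to-face | superior | wrong | right |
| face-to-face − video | inferior | wrong | right |
| face-to-face − video | superior | right | wrong |

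No combination is right for both.

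**3. Numerical example.** Assumed: dQ = 0 without error, standard error of the cost difference 60. Then NB = −dC, and the half-width is 1.96 × 60 = 117.6.

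- Video 200 cheaper: cost interval −317.6 to −82.4; net-benefit interval +82.4 to +317.6. The printed rule labels video inferior on net benefit, although the interval favours video.
- Video 200 dearer: cost interval +82.4 to +317.6; net-benefit interval −317.6 to −82.4. The printed rule labels video inferior on cost but not on net benefit. It should be inferior on both.

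With dQ = 0 the value of λ does not matter.

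**4. How often would it misfire?** Inputs:

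- 167 per arm, from the Sample size calculations section (197 less 15% loss: 197 × 0.85 = 167.45).
- Assumed: cost SD 500 per arm, video truly 200 cheaper, equal mean QALYs, λ = 50,000, costs and QALYs independent.

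Standard error of NB = √[(λ × SD_Q)² + 500²] × √(2/167), and √(2/167) = 0.1094. The chance that the lower limit exceeds zero is P(Z > 1.96 − 200/SE).

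| QALY SD | SE of NB | 200/SE | By formula | Simulated (4,000 trials) |
|---|---|---|---|---|
| 0 | 54.7 | 3.66 | 96% | 96% |
| 0.02 | 122.4 | 1.63 | 37% | 36% |
| 0.12 | 658.9 | 0.30 | 5% | 5% |

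In these settings the rule labels video inferior on cost in 0% of trials.

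Which row is most relevant? The article's margin of 0.08 is said to be half an SD, so it implies an AQoL-6D SD of 0.16. Over 9 months that is about 0.16 × 0.75 = 0.12 QALYs, if a participant's utility stays constant and before any baseline adjustment. The last row is therefore nearest the article's own figure. Baseline adjustment would reduce the SD and move the result towards the middle row.

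**The case against.** **Net benefit may not be calculated in the example above.** The economic section can be read as computing QALYs by area under the curve, cost per QALY and net benefit only when one mode is better on effect but also dearer. With equal QALYs and video cheaper, that condition is not met, and on this reading nothing would be labelled. This stands as a limit on the example, so it cannot be said flatly that a cheaper video arm would be called inferior. It does not rescue the rule. If video is better and dearer, a net-benefit interval above zero means that its extra QALYs are worth more than its extra cost. If face-to-face is better and dearer, the same interval means that video's saving outweighs the QALYs lost. In both cases the rule labels video inferior. The decision sentence itself also names net benefit without repeating the restriction.

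**The misfire may be uncommon.** This also stands. It requires the whole net-benefit interval to lie above zero, which in the illustration happened in only 5% of trials at the QALY SD nearest the article's.

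**The formula is printed and a health economist oversees the work, so the slip would probably be noticed.** That is fair, and it lowers the practical risk. It does not make the written rule correct.

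A reader might infer two stronger claims that the article does not support:

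- *That a cost saving could not be claimed.* The primary economic evaluation is the between-group difference. A two-sided interval for cost lying wholly below zero shows a saving, and nothing forbids reporting it. The article merely gives no explicit criterion for it.
- *That travel costs are wrongly left out.* The aims name "cost-effectiveness (participant-level travel time and travel-related costs, health care usage"), and the economic section singles out only patient time for its extra analysis: "In a secondary analysis, the cost of patient time will be included as an additional cost component". But that section opens with direct and indirect costs and gives no closed list of components. An article commonly leaves costing detail to the full plan. Nothing in the article shows travel to be the main patient cost that differs between modes.

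**Conclusion.** The point holds as a defect in a stated decision rule. By the article's own definition of net benefit, one shared bound and label cannot be right for both cost and net benefit. With video minus face-to-face, the rule is right for cost and reversed for net benefit. This conclusion needs no outside figure and does not depend on the order of subtraction.

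The consequence is limited. It is confined to the economic evaluation: the co-primary analyses, their margins and the sample size do not use this rule. The misfire frequency of 5% to 96% rests on the assumed cost SD, saving and λ, and above all on QALY variability. Those percentages illustrate the range and do not forecast this trial.

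**What to change.** State in the Economic evaluation section that all differences are video minus face-to-face, and replace the shared criterion with two, each based on the two-sided 95% CI:

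- **Cost:** video is dearer (inferior) if the lower limit is above zero, and cheaper if the upper limit is below zero.
- **Net benefit:** video is superior if the lower limit is above zero, and inferior if the upper limit is below zero.

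The same edit could say whether net benefit is calculated in every case or only when the better mode is also the dearer one, since the present text can be read either way.

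The cost is the rewording of one paragraph. No new data, sample size or analysis method is needed. The article already provides for a dated, explained log of amendments to the analysis plan, and the change can be recorded there before the economic data are analysed.

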### Patient and public involvement

No patients were involved in setting the research question. Patients with knee OA were involved in i) review of the plain language statement and consent form, particularly the text related to limited disclosure; ii) review and completion of the electronic outcome measurement survey; iii) testing the participant instructions for, and use of, the wearable activity tracker; iv) testing participant instructions for, and use of, Zoom for video-conferencing; v) review of other participant resources (Osteoarthritis Information, Exercise Booklet) and the Appointment Log Book used in data collection; vi) creation of telehealth training videos for the physiotherapist e-learning modules, and exercise videos/photographs for the website/Exercise Booklet, as patient actors; and vii) review of study logo. Patients provided feedback to the research team about information content, presentation and readability, as well as time taken to complete the outcome measurement survey. Patients with knee OA also participated in pilot “practice consultations” with the trial physiotherapists as part of the physiotherapist’s training procedures.

Representatives of the national physiotherapy professional body (Australian Physiotherapy Association) were involved in designing the trial (including selecting outcome measures) and obtaining funding. The Australian Physiotherapy Association assisted in physiotherapist recruitment by advertising for physiotherapists to participate in the trial via member electronic communications. Physiotherapists (not otherwise involved in the trial) i) reviewed the exercises contained within the “Exercise Booklet” and suggested the addition of three new balance exercises; ii) reviewed and provided feedback on the physiotherapist “Zoom Troubleshooting” resource embedded within the e-learning modules and physiotherapist trial manual; and iii) performed as actors/models in the creation of telehealth training videos for the physiotherapist e-learning modules.

The trial protocol underwent independent review by the ANZMUSC Clinical Trials Network, which included a written submission and a verbal presentation in an open forum to ANZMUSC members, review by two members from each of the Scientific Advisory Committee and the Consumer Advisory Group. The trial was endorsed by ANZMUSC on 25/07/2019, indicating its high priority and quality, importance to consumers/patients, clinicians and policy makers, and its potential to improve patient outcomes.

